#### Sampling

Sample size was estimated based on two possible outcomes. First, to detect a difference of 2 points in the RESVECH 2.0 scale mean scores [37] between the intervention and the control group with a standard deviation of 2.0 (5% type 1 error and 20% type 2 error) based on data published by Castro et al. who found a reduction of 8 points in RESVECH 2.0 at 4 weeks of treatment (this is a 23% reduction) [24]. We used a 2-point reduction for sample estimation as the minimum clinically significant difference, and so the study was powered enough to detect just this small difference. The required sample size for this is 17 patients per group. Second, the time to achieve a 50% reduction of the wound area, estimating an average of 49.5 days in the control group and 30.0 days in the intervention group with a standard deviation of 20.0 days (5% type 1 error and 20% type 2 error), as based on the study by Lee [38]. The required sample size for this is 18 patients per group.

An additional 30% is added to compensate possible loss of patients in follow-up, and so the final sample size is 54 patients (27 patients in each group). It is expected that each one of the three health care centres will recruit 18 patients for the study.

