### Data analysis plan

A researcher who is blinded to group allocation will perform the data analysis. All analyses will be performed with SPPS Statistics software (IBM Corp., Armonk, NY, USA). Data will be expressed as frequency and percentages for categorical variables, and mean, standard deviation, range and median for quantitative variables depending on the distribution (normality will be checked with the Shapiro–Wilk test). The statistical significance level will be set at *P* < 0.05.

For the primary outcome of improvement in wound healing the wound area reduction at 8 weeks in the intervention group compared with the standard care group will be tested by a difference of means test. The increase in RESVECH 2.0 [37] score at 8 weeks between both groups will be examined by a difference of means test (*t* test for independent groups or Mann–Whitney test depending if variables adjust to a normal distribution). The effect size will be estimated by Cohen’s *d* statistic. In addition, a repeated-measures analysis (analysis of variance or Friedman test) and a survival analysis (Kaplan–Meier) will be used to analyse the evolution over time.

For secondary outcomes, proportions and categorical variables will be tested using a chi-squared test, and continuous variables will be tested using a mean difference test (parametric or nonparametric).

Analyses will be performed between groups as randomized (an intention-to-treat analysis). Missing data for the outcomes will be tested if they are missing at random; otherwise the last observation carried forward approach will be used for imputation [43]. Furthermore, sensitivity analyses over all the completed cases (a per-protocol analysis) will be performed to check for inconsistencies.

A subgroup analysis by wound type will also be performed to explore whether the effect of the intervention differs for any type of wound according to its aetiology. Moreover, another subgroup analysis by primary care centre will be carried out to check if there are any differences in outcomes according to the centre.

No interim analyses or formal stop-study rules are planned; no harmful problems are anticipated for patients because this new dressing has been previously tested in a series of patients with wounds of various aetiologies without any serious adverse effects [35].

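### The stated 80% power describes patients with an observed week-8 RESVECH score; power of the primary intention-to-treat analysis was not worked out and may be well below 80% if last observation carried forward is used

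*Protocol article*

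**What the plan says.** Protocol article, Sampling: the RESVECH 2.0 calculation aims to detect "a difference of 2 points in the RESVECH 2.0 scale mean scores", working "with a standard deviation of 2.0", at "5% type 1 error and 20% type 2 error", and arrives at 17 per group. A second calculation, for time to a 50% reduction in wound area (30.0 v 49.5 days, SD 20.0), arrives at 18 per group; the Outcomes section lists that end point as secondary. The loss allowance follows: "An additional 30% is added to compensate possible loss of patients in follow-up, and so the final sample size is 54 patients (27 patients in" [...], that is, 27 per arm. The only level of change mentioned is from a cited series, "who found a reduction of 8 points in RESVECH 2.0 at 4 weeks of treatment".

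Protocol article, Data analysis plan: the primary RESVECH comparison is a two-group test of the 8-week change (t test or Mann–Whitney). The analysis set is fixed by "Analyses will be performed between groups as randomized (an intention-to-treat analysis"). Missing outcomes are first checked for being missing at random; "otherwise the last observation carried forward approach will be used for imputation". What is done when the check passes is not stated. Completed cases are analysed only as a sensitivity analysis.

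**The concern.** A loss allowance of this kind protects power when lost patients contribute nothing and the remaining ones show the full planned effect. The main analysis here keeps all 27 per group. If carry-forward is triggered, a lost patient enters the week-8 comparison with an earlier, smaller change. This lowers the mean difference below 2 points. It also mixes small early changes with full week-8 changes, which pushes the SD above 2.0. Enrolling more patients at the same loss rate raises the count but leaves the reduced standardized effect where it was.

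The planned difference and SD were not adjusted for this, so the 20% type 2 error belongs to a set of patients that does not carry the primary conclusion. The practical risk lies in a null intention-to-treat result. Sampling calls 2 points the smallest clinically significant difference and says the study is powered for it, so a null result could be read as ruling that difference out when the power to see it was never calculated.

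**Working it through.** **Inputs from the protocol article.** Difference 2 points, SD 2.0, 5% type 1 error, 80% power, 27 per group and a 30% loss allowance (Sampling); visits at weeks 2, 4, 6 and 8 (Data collection and management). A two-sided test is assumed, since it reproduces the printed sizes.

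**The plan's own figures.** Two-sample t test:
- RESVECH, standardized effect 2/2.0 = 1.0: n = 16.7, so 17 per group (power 0.807).
- Time to 50% area reduction, 19.5/20.0 = 0.975: n = 17.5, so 18 per group (power 0.811).
- After loss: 27 × 0.7 = 18.9 per group; RESVECH power 0.849 at effect 1.0.

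Both sizes reproduce, and the allowance does what was intended for completers.

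**Power if carry-forward is applied.** Let each patient's week-8 change be normal with arm mean m and SD 2.0. Let w = 1 for a patient who stays (70%) and w = f for one who is lost (30%), where f is the share of the week-8 change reached at the last visit. Then
- mean difference = 2 × E[w];
- variance in an arm = E[w²] × (4 + m²) − (E[w] × m)².

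Assumptions not in the document: arm means, linear course, equal loss in both arms, and timing of loss. The 8 v 6 case borrows the 8-point figure, which is a 4-week result, for week 8 and sets control 2 points lower.

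Worked case, 8 v 6, last visit spread evenly over weeks 0, 2, 4 and 6 (f = 0, 0.25, 0.5, 0.75):
- E[w] = 0.7 + 0.3 × 0.375 = 0.8125, so the difference is 1.625.
- E[w²] = 0.7 + 0.3 × 0.21875 = 0.7656.
- Variance, intervention: 0.7656 × 68 − 6.5² = 9.81 (SD 3.13). Control: 0.7656 × 40 − 4.875² = 6.86 (SD 2.62).
- Pooled SD √8.34 = 2.89; standardized effect 1.625/2.89 = 0.56; power at 27 per group about 53%. Simulation gives 52% to 53% (Mann–Whitney 57%).

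All losses straight after baseline (f = 0): difference 1.4; variances 0.7 × 68 − 5.6² = 16.24 and 0.7 × 40 − 4.2² = 10.36; pooled SD 3.65; effect 0.38; power 28%.

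| Case (27 per group, t test) | Loss | Power |
|---|---|---|
| Completers only | 30% | about 85% |
| 8 v 6, linear, all lost after baseline | 30% | about 28% |
| 8 v 6, linear, last visit weeks 0–6 | 30% | about 53% |
| 8 v 6, linear, last visit weeks 2–6 | 30% | about 67% |
| 8 v 6, linear, all lost after week 6 | 30% | about 91% |
| 8 v 6, plateau by week 4, last visit weeks 0–6 | 30% | about 64% |
| 8 v 6, plateau by week 4, last visit weeks 2–6 | 30% | about 87% |
| 4 v 2, linear, last visit weeks 0–6 | 30% | about 82% |
| 8 v 6, linear, last visit weeks 0–6 | 20% | about 65% |
| 8 v 6, linear, last visit weeks 0–6 | 10% | about 79% |

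Simulated values move by one or two points between runs.

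**The case against.** The arithmetic of the sample size is sound, and inflating a completer number for loss is ordinary practice. The article does not claim that the 80% was computed under carry-forward. Three further objections carry weight.

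First, carry-forward is only one branch of a conditional rule, and the detail of the other branch may sit in an analysis plan that is not shown. A reader might infer that the primary end point simply fails to have its stated 20% type 2 error. The document does not support that: it depends on the check failing and on when patients leave. Still, carry-forward is the only imputation named, and the Participants section withdraws patients for wound worsening, so missingness linked to outcome is plausible.

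Second, a reader might take the 53% case and say the trial would miss a real 2-point difference about half the time, or that true power is 50% to 70%. Neither is established. The 8 points is a 4-week figure from a cited series, no control change is given, and a linear course to 8 points at week 8 would mean only 4 points at week 4. Earlier improvement, later loss or smaller changes bring power to 80% or more.

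Third, 30% is an allowance and not a forecast; at 10% loss even the linear, evenly spread case stays near 80%. Patients who leave follow-up because the wound has healed are not diluted by carrying their score forward.

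These points limit the size of the claim. They do not remove the mismatch between the set that was powered and the set that is primary.

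**Conclusion.** The concern holds in a limited form. The stated type 2 error applies to about 17 to 19 patients per group with an observed week-8 RESVECH change: 17 is the RESVECH requirement, 18 belongs to the secondary time-to-50% outcome, to which this change-score argument does not directly apply, and about 19 is what 27 leaves after 30% loss. For the primary intention-to-treat comparison, power in the carry-forward branch was not computed and may be well below 80%.

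At 30% loss the illustrations run from about 28% to 91%. Only the SD, the 2-point difference, the group size and the 30% come from the document. The arm means, the course of healing, the timing of loss and equal loss between groups are assumptions, and withdrawal for worsening could make loss unequal and move the effect in either direction. The conclusion is that power is unknown and possibly low, not that any one figure in the table is the trial's power.

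**What to change.** Keep 54 patients and the visit schedule.

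1. In Sampling, say that the 80% applies to about 18 to 19 completers per group, and that 17 is the RESVECH requirement.
2. In the Data analysis plan, make the primary RESVECH analysis a likelihood-based repeated-measures model on the scores observed at weeks 2, 4, 6 and 8, with the week-8 group difference as the estimate. Use carry-forward at most as a sensitivity analysis. The model assumes that loss is explained by the scores already observed, which should be stated given the withdrawals for worsening.
3. If carry-forward stays in the primary analysis, report intention-to-treat power by simulation as a range over early and late loss, and say that a null result does not exclude a 2-point difference. Do not then describe the 30% addition as making up for losses.

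The cost is a short simulation, reworded text and a little more analysis work on data already being collected. The downside is a less favourable stated power. The change should be fixed before the allocation is unblinded.

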### Randomization and blinding

Patients (*n* = 54) will be randomized into an intervention group (antioxidant dressing) or control group (standard clinical practice using dressings that create a moist environment). The block randomization scheme was generated using the EPIDAT software. Participants will be randomized to receive antioxidant dressing or standard wound dressing with a 1:1 allocation ratio (Fig. 2) using stratified block randomization with a fixed block size per centre. Once the patient has agreed to participate and has been shown to meet the inclusion criteria, the clinical nurse will open opaque closed envelopes sequentially numbered containing a sheet (folded four times) with the group allocation. Neither the patient nor the clinical nurse is blinded to the treatment received; the data and the wound pictures will be codified and the assessor who evaluates the wound pictures and the data analyst will be blinded to the treatment.

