### Intervention and control

The REOX study has two arms (see Fig. 2). Both arms included cleansing with saline solution and debridement to remove devitalized tissues, if needed, according to recommendations from clinical practice guidelines.

In the intervention group, the antioxidant dressing will be applied over the wound bed and covered with a secondary adhesive dressing. The dressing will be kept in place for 2 to 3 days, according to the recommendations of the manufacturer.

In the control group (standard practice), a dressing that creates a moist environment will be applied over the wound bed (such as hydrocolloid, alginate, polyurethane foam or silver dressing, according to the nurse’s judgement and the availability of the products at the centre) and covered with a secondary adhesive dressing if necessary. The dressing will be kept in place for 2 to 3 days, according to the recommendations of the manufacturer.

To improve the adherence of the patients to the treatment (both groups), the clinical nurse who treats the patients will reinforce in each dressing change how important it is to keep the dressing in place until the next visit, and explain to the patient that if they are experiencing pain, itching or other wound-related symptoms, they should consult with the nurse but not remove the dressing. Any dressing-related symptoms will be recorded as a possible adverse effect.

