### Oversight and monitoring

The project team at the University of Jaén is responsible for the design, preparation and coordination of the trial, including the dissemination of the results. This team meets every month to discuss the progress of the trial and to solve any arising problems. A steering committee, formed by two professors from the Nursing Department of the University of Jaén and a member of Histocell, will supervise the trial. This committee will meet twice a year during the course of the study and when the data collection is complete. At each primary care health centre participating in the study a clinical nurse will be responsible for recruiting patients, obtaining informed consent and coordinating the trial at the site. In addition, some site visits are planned every 3–4 months to audit the trial and monitor compliance with the study design. Regular reports with data on recruitment and follow-up rates will be sent to the principal researcher every month. Any deviation from the protocol will be fully documented by a breach report. Any significant amendments to the protocol will be communicated to the relevant parties and updated in the trial register.

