## Trial status

The study is registered on ClinicalTrials.gov (NCT03934671), https://clinicaltrials.gov/ct2/show/NCT03934671, registered on 2 May 2019. The Ethics Committee of Jaén approved the study in April 2019 with reference number 0645-N-19. This protocol is version 2.0, April 2020. Recruitment began in September 2019. The expected date for recruitment completion is December 2020.

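### A fixed block size within each centre makes the ends of blocks predictable to unblinded recruiting staff, an avoidable risk of selection bias at enrolment

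*Protocol article*

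**What the plan says.** The Randomization and blinding section of the protocol article allocates patients "with a 1:1 allocation ratio" by "stratified block randomization with a fixed block size per centre". After consent and confirmation of eligibility, "the clinical nurse will open opaque closed envelopes sequentially numbered containing a sheet (folded four times) with the group allocation". The same section states: "Neither the patient nor the clinical nurse is blinded to the treatment received". Blinding is confined to the assessor of the photographs and the data analyst.

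The Oversight and monitoring section says that at each centre "a clinical nurse will be responsible for recruiting patients, obtaining informed consent and coordinating the trial at the site". The Intervention and control section refers to "the clinical nurse who treats the patients will reinforce in each dressing change". The Sampling section expects 18 patients from each of three centres, 54 in all. The Trial status section dates the protocol (version 2.0) to April 2020, with recruitment open since September 2019, and adds: "The expected date for recruitment completion is December 2020".

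The block size is not given. Nothing in the article provides for varying sizes, for allocation away from the site, or for withholding the size from site staff.

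**The concern.** Concealment has two parts: hiding the next sheet, and preventing its deduction from earlier ones. Opaque numbered envelopes do the first. With a constant block size in a short, open sequence, the second fails. In every block the last allocation, and sometimes more than one, is fixed by those before it. Opening the envelope only after consent does not help, because the arm can be foreseen before the patient is approached.

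The stake is comparability at baseline. Eligible wounds run from 1 to 250 cm² and cover several aetiologies, and randomization is stratified by centre only. Whoever decides whom to approach, and when, could steer prognosis towards one arm, even unconsciously. The Discussion section itself warns that an imbalance in wound type could confound the results. Blinded photograph reading and blinded analysis come after enrolment and cannot undo a selection already made.

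**Working it through.** **Inputs from the article.** 1:1 allocation, one fixed block size, three centre lists of 18 patients. RESVECH SD 2.0 and a minimum clinically significant difference of 2 points (Sampling section).

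**The plan's own figure.** An exact two-sided t-test calculation (5% level, 80% power) gives 17 per group for RESVECH and 18 per group for time to 50% area reduction, as stated. Allowing for 30% loss, 18/0.7 = 25.7, so 26 per group against the planned 27. The sample size is not in dispute; it only fixes the list length, 54/3 = 18.

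**Certain allocations.** In a permuted 1:1 block of size 2m, the expected number of allocations determined by the earlier ones is 2m/(m + 1).

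- Block 2: 1.0 per block, 9 blocks per centre, 3 × 9 × 1.0 = 27 of 54.
- Block 4: 1.333 per block. A list of 18 holds four full blocks plus two patients who are never certain, so 3 × 4 × 1.333 = 16 of 54.
- Block 6: 1.5 per block, 3 × 3 × 1.5 = 13.5 of 54.
- One block of 18: 1.8 per block, 3 × 1.8 = 5.4 of 54.

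Always naming the arm with more places left is right in about 75%, 71%, 68% and 62% of cases over complete blocks of 2, 4, 6 and 18, against 50% under simple randomization.

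**From predictability to bias (assumption).** Suppose that only at certain positions the patients enrolled have an expected change d/2 better when the coming arm is one treatment and d/2 worse when it is the other. With F certain positions and 27 patients per arm, the expected arm difference under no treatment effect is (d/2) × F/27 = d × F/54. Its standard error is about 2 × √(2/27) = 0.54 points. Rejection rates below come from simulation (3 × 18 patients, SD 2, no true effect, all patients analysed, two-sided 5% t-test).

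| Block | Size known from | F | Bias, d = 2 | Rejection, d = 2 | Bias, d = 1 | Rejection, d = 1 |
|---|---|---|---|---|---|---|
| 2 | start | 27 | 1.00 | 42% | 0.50 | 15% |
| 2 | after 3 blocks | 18 | 0.67 | 21% | 0.33 | 9% |
| 4 | start | 16 | 0.59 | 18% | 0.30 | 8% |
| 4 | after 2 blocks | 8 | 0.30 | 8% | 0.15 | 5–6% |
| 4 | after 3 blocks | 4 | 0.15 | 6% | 0.07 | 5% |
| 6 | start | 13.5 | 0.50 | 14% | 0.25 | 7% |
| 6 | after 2 blocks | 4.5 | 0.17 | 6% | 0.08 | 5% |
| 18 | start | 5.4 | 0.20 | 7% | 0.10 | 5–6% |

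A block of 6 leaves nothing to exploit if three blocks are needed to learn it, because 3 × 6 = 18 is the whole list.

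**Effect of varying the sizes.** For 18-patient lists and a guesser who knows the possible sizes but not their order, the certain share is about 6% for sizes 4/6, 4% for 2/4/6 and 2% for 4/6/8. Over complete fixed blocks it is 33% (size 4) or 25% (size 6). The best-guess hit rate barely moves: 67–70% against 68–71%.

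**The case against.** The strongest objection is that the larger figures need a nurse who knows the block size at the first patient. The article does not say that the size is disclosed. If it must be inferred from 18 patients, learning consumes much of the list, and for blocks of 4 or 6 the rejection rate falls close to nominal. This stands, and the figures for a size known from the start are upper figures. The size could also be 18, one block per centre, where little is predictable.

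The steer is also a strong assumption. Two points is one SD and the whole minimum clinically significant difference. Recruiting 18 patients per centre over the 16 months from September 2019 to December 2020 is about one a month, so the article shows no pool of waiting patients to choose from. This limits the likely size of any bias but does not remove the route to it.

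A reader might infer that one named nurse per centre recruits, randomizes, treats and assesses. The article assigns these tasks to a clinical nurse without saying that it is the same person. The shared role is plausible, and staff at one small centre could in any case see earlier allocations, but it is not stated. A reader might also infer that selection has occurred or that the true error rate is 42%. The article supports neither.

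**Conclusion.** The design weakness holds. The article names a fixed block size, the more predictable option, and puts the envelopes in the hands of unblinded site staff in a role that also recruits. Some allocations can then be foreseen, chiefly at block ends; by no means all can.

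The size depends on three things the article does not give: the block size, whether it is known or must be learned, and how far prognosis could be steered. Blocks of 2 would be a material exposure even after learning (about 0.7 points and 21% rejection with a 2-point steer). Blocks of 4 or 6 matter if the size is known, and add little if it has to be learned (about 0.15 to 0.3 points, 5% to 9%). This is a risk, worth removing because removal is cheap; it is not evidence that the trial is biased.

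**What to change.** For envelopes not yet used, replace the list with permuted blocks of randomly varying size within centre. The university team, which already has design and preparation, would generate it, and the sizes would be withheld from site nurses. State this in the protocol. Opening after consent and eligibility is already specified; add that baseline measurements are recorded on the case report form before the envelope is opened.

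The change removes most certain predictions but not informed guessing, as the unchanged hit rate shows. It costs a new list and envelopes for the remaining patients, a sentence or two of protocol text, and a possible final imbalance of one to three patients per centre. Patients already enrolled when the list changes are not covered.
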